# STUDY DESIGN

The proposed study is a double-blind, randomized controlled trial of permethrin-treated *lesus* to prevent *P. falciparum* malaria in children 6–18 months of age at study enrollment conducted at two sites in rural western Uganda. Participants will be randomized to one of two arms: permethrin-treated (intervention) or untreated (control) *lesus.* Participating mother-infant pairs will receive a new LLIN and two permethrin-treated or untreated *lesus* at enrollment. The total sample size will be 400 mother-infant pairs with 200 pairs in each arm. We will follow participants longitudinally for six months. Participants will be instructed and incentivized to present to one of the two study clinics when a fever develops, where they will be evaluated, tested, and treated, if positive, for malaria. Participants will also attend scheduled clinic visits every two weeks for routine surveillance of adverse effects and to test for asymptomatic infection. Re-treatment and sham re-treatment of *lesus* will occur each month.

# STUDY ENROLLMENT AND WITHDRAWAL

## Subject Inclusion Criteria

In order to be eligible to participate in this study, an individual must meet all of the following criteria:

- Provide signed and dated informed consent form (ICF)
- Willing to comply with all study procedures and be available for the duration of the study
- Female of any age with a child 6 to 18 months of age at the time of enrollment
- Resident of village located in Bugoye, Maliba, or Mubuku sub-counties. Recruitment will initially focus on residents of villages within 2 km of study clinics in order to facilitate attendance, but we will not restrict enrollment to residents of these villages.

## Subject Exclusion Criteria

An individual who meets any of the following criteria will be excluded from participation in this study:

- Mother or child taking any malaria chemoprevention regimen, including individuals living with HIV or exposed children who are taking cotrimoxazole
- Child with known sickle cell disease
- Known allergic reactions to components of the study product(s)
- Treatment with another investigational drug or other intervention
- Anything that would place the individual at increased risk or preclude the individual’s full compliance with or completion of the study.

## Strategies for Recruitment and Retention

### Sensitization Meetings

Prior to study implementation, we will conduct a series of sensitization meetings with leaders including clinical staff at local health facilities, village chairpersons, and community health workers (CHWs) to disseminate information about the study aims, methods, and anticipated risks/benefits of participation. There will be ample opportunity for attendees to ask questions and provide feedback. We will ask CHWs to distribute information about the study to eligible women in their respective coverage areas, including the date and time of informational meetings for interested women.

### Information Sessions

At the informational meeting conducted in the village, study staff fluent in the local language (e.g., Lukhonzo), will describe the study aims, methods and anticipated risks/benefits of participation in a group setting. Women who are interested in participating will move to a private area where they will have an opportunity to ask additional questions. Study staff will confirm eligibility criteria and record the individual’s address and preferred contact information to schedule a household visit. On the agreed upon date, a study staff member will travel to the household and ask the individual to provide written consent for participation, which will be immediately followed by the initial household survey.

### Participant Incentives

Participants will be eligible to receive the following incentives for participation:

| Event | Eligibility | Amount (UGX* / USD) |
| --- | --- | --- |
| Baseline Home Visit | Visit Completed | 10,000 / $3.00 |
| Bi-Weekly Study Visit (12) | Attends Visit (Transport Supplement) | 8,000 / $2.25 |
| Bi-Weekly Study Visit (12) | Communication Supplement | 2,000 / $0.60 Airtime |
| Bi-Weekly Study Visit (12) | Completed *Lesu* Use/Wash Diary | In-Kind (e.g., Soap, Sugar) |
| Final Visit / Exit Interview | Attended ≥80% of visits | 20,000 / $6.00 |
| **POTENTIAL TOTAL** | | 180,000 / $50.00 |

**Approximate UGX to USD conversion; may change based on exchange rate*

### Contacts

On enrollment, participants will be asked to provide the best contact information, including a mobile phone number, if available. Study staff will confirm if this phone is owned/used by the participant or belongs to someone else (e.g., neighbor, relative). In addition, we will ask for permission to send reminders for upcoming study visits via text or phone call. If a participant confirms attendance, then no further contact will be made. Participants will receive cellular airtime credit for this purpose (see Section 4.3.3). Study staff will make up to three text or phone contacts prior to a scheduled study visit.

If study staff are unable to confirm attendance after three attempts, staff will contact the CHW responsible for the area and request assistance contacting the participant, which may include up to three visits to the home. Similar procedures will be used to contact participants after a missed visit.

## Treatment Assignment Procedures

### Randomization Procedures

Participants will be randomized in a 1:1 ratio between intervention and control arms with randomization stratified by age group (age 6–11 months and 12–18 months) and by study site (Bugoye and Malaiba sub-counties). We will utilize stratified randomization to ensure an even distribution between arms at each clinical site and within each age group. Blocks will be variable in size to ensure allocation concealment. The randomization protocol will be developed and implemented by a University of North Carolina at Chapel Hill (UNC) biostatistician not involved in the direct enrollment of participants. Statistical software will be used to generate the list of random assignments with a 1:1 ratio. The randomization sequences will then be uploaded to the Research Electronic Data Capture (REDCap) database. Participants will be randomized upon enrollment using the REDCap Randomization Module on portable tablet devices equipped with cellular internet capability. Participants and health center staff but not research staff will be blinded to the allocation. Sham treatments and re-treatments of *lesus* will be employed to maintain blinding.

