## Study Outcome Measures

| **Study Measure** | **Method of Collection** |
| --- | --- |
| 1. Primary Outcome |  |
| 1.A. Incidence of clinical malaria in child | (1) Acute febrile illness AND positive RDT at scheduled or unscheduled study clinic visit  - or -  (2) Written documentation of fever AND positive RDT from non-study clinic visit |
| 2. Secondary Outcomes |  |
| 2.A. Change in child’s Hb level | Hb measured at baseline (Week 0), Week 12, and Week 24 visits using HemoCue® device. |
| 2.B. Change in child’s growth measures | Height, weight, measured at baseline (Week 0), Week 12, and Week 24 visits. |
| 2.C. Change in child’s nutritional status | MUAC measured at baseline (Week 0), Week 12, and Week 24 visits [22]. |
| 2.D. Asymptomatic parasitemia in children | Presence of malaria parasites on bi-weekly dried DBS as determined by qPCR. |
| 2.E. Hospitalization for malaria | Self-reported history of hospitalization on bi-weekly questionnaire AND confirmation by study staff. |
| 2.F. Clinical malaria in mother | Same as 1.A. |
| 2.G. Change in mother’s Hb level | Same as 2.A. |
| 2.H. Burden of care-seeking | Self-reported history of clinic visits, work days missed, health expenditures on bi-weekly questionnaires. |
| 3. Safety Measures |  |
| 3.A. Adverse reaction to treated-*lesu* | Self-reported history on bi-weekly questionnaire and confirmation by clinical staff. |
| 3.B. Severe adverse event (SAE) | Care-seeking, hospitalization, or death attributable to the intervention. |
| 4. Covariates of Interest |  |
| 4.A. Socioeconomic status | Questions from baseline survey on ownership of mobile phone, vehicle, etc. [34] |
| 4.B. Maternal education | Self-reported history on baseline questionnaire. |
| 4.C. Frequency of *lesu* use and washing | Self-reported history on bi-weekly questionnaire, use diaries, direct observation. |
| 4.D. Residual permethrin levels | Punches of *lesu* cloth taken at 2-, 4-, 6-month visits tested by gas chromatography [35] |
| 4.E. *Anopheles* mosquito density | CDC light trap collections in peri-domestic space (indoor/outdoor) with species identification |

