### Masking Procedures

Study participants and clinical providers will remain blinded to allocation of the intervention until database lock. Initial treatment and monthly re-treatment of lesus will be performed with either 0.5% permethrin or water (i.e., sham treatment) in order to maintain blinding. Study staff involved in re-treatment (permethrin or sham) of lesus will be unblinded.

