## Administration of Intervention

Treatment of *lesus*, either with permethrin or sham, will take place during in-person visits. No treatments or re-treatments will take place outside this setting. Study staff responsible for treatment and re-treatment, who will be unblinded to the intervention, will confirm the group assignment against randomization table prior to treatment and re-treatment. During treatment or sham treatment, each ziploc bag will be labeled with the study ID to prevent confusion.

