## Unscheduled Visits

Participants will be instructed to present to their respective study clinic for any acute febrile illness or other symptoms that may be consistent with malaria (e.g., poor feeding, headache, malaise). Upon registration, participants will present their study ID card to health center staff, who will subsequently notify study staff of the visit. Participants will undergo routine evaluation, testing, and treatment in accordance with local protocols. At the conclusion of the visit, a staff member will interview the patient to document symptoms and review clinic and laboratory registers to abstract relevant information. Of note, the study will maintain a modest supply of RDTs and artemether-lumefantrine (AL) to ensure there is no shortage of diagnostic tests or treatment.

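### Section 4.4.1 leaves research staff unblinded without limit, a wider group than in 4.4.2 and 5.7, and no section blinds the study staff who record fever for the primary endpoint

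*Protocol*

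**What the plan says.** Section 3 gives the design: "The proposed study is a double-blind, randomized controlled trial". Three sections then describe who knows the allocation.

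- **4.4.1 Randomization Procedures:** "Participants and health center staff but not research staff will be blinded to the allocation". The term research staff carries no qualifier.
- **4.4.2 Masking Procedures:** "Study participants and clinical providers will remain blinded to allocation of the intervention until database lock", and "Study staff involved in re-treatment (permethrin or sham) of lesus will be unblinded".
- **5.7 Administration of Intervention:** the unblinded group is "Study staff responsible for treatment and re-treatment, who will be unblinded to the intervention".

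Section 2.2 defines the primary outcome in children. Its first route is "1) Acute febrile illness AND positive RDT at scheduled or unscheduled study clinic visit"; its second is written evidence of fever and a positive RDT from a clinic outside the study.

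Section 7.1.3 has study staff take axillary temperature at each visit. Sections 6.4 and 7.1.1 add an interval history at the two-weekly visits that covers fever and other malaria symptoms. For acute visits, section 6.6 has health center staff notify study staff, after which "a staff member will interview the patient to document symptoms and review clinic and laboratory registers to abstract relevant information".

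**The concern.** A research assistant who never treats a cloth is unblinded under 4.4.1. Under 4.4.2 and 5.7 the same person is not named as unblinded and could be blind. The protocol does not settle which applies, and it uses research staff, study staff, clinical staff, clinical providers and health center staff without defining them.

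The gap touches the primary endpoint. The RDT half of the case definition is a test result. The fever half depends on a temperature reading, a reported history and what is abstracted from a register. If the person making those entries knows the arm, a child with a positive RDT could be classified differently in the two arms. The planned analysis cannot repair that afterwards: the robust variance in 10.3.1 deals with overdispersion, and the multiple imputation in 10.3 deals with missing data.

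**Working it through.** The protocol gives no figure on this point, so the check is a comparison of text, followed by one illustration.

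**1. Who is blinded.** Participants are blinded in 4.4.1 and 4.4.2. Health center staff (4.4.1) and clinical providers (4.4.2) are blinded too. The sections agree so far.

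**2. Who is unblinded.** 4.4.1: research staff, without limit. 4.4.2: staff who re-treat. 5.7: staff who treat and re-treat. The last two groups lie within the first. The status of all other research staff is therefore unblinded in 4.4.1 and unstated in 4.4.2 and 5.7.

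**3. Who records fever.**
- Temperature: study staff (7.1.3).
- Interval symptom history: staff (7.1.1, 6.4). In the pilot, research staff gave the corresponding questionnaire (1.2), and section 2.1 says the trial uses similar methods.
- Interview and register abstraction after acute visits: an unspecified staff member (6.6). The preceding text suggests study staff but does not say so.

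**4. Is there a safeguard elsewhere?** None was found. No section blinds these recorders or separates them from the treatment staff. Randomization runs in REDCap on tablets (4.4.1) and is marked at the home visit (Appendix A1). Study data are also entered on tablets into a database such as REDCap (14.2), with no stated restriction on who sees the allocation. Re-treatment falls on the same clinic days as history and temperature (6.4), and 5.8 requires all staff to show proficiency in treating the cloths. Overlap of roles is thus possible in practice.

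**5. Where the exposure is limited.** Evaluation and testing at acute visits follow local routine (6.6), which reads as the work of blinded health center staff. No RDT is listed among the two-weekly activities in 6.4, and Appendix A2 places follow-up RDTs at acute visits. Section 2.2 does count cases at scheduled visits, so that route stays open but needs a further testing step.

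**6. Illustration, on an assumption that is not in the documents.** Suppose a share q of cases goes unrecorded in one arm only. If that is the intervention arm, observed rate ratio = true rate ratio × (1 − q). If it is the control arm, observed rate ratio = true rate ratio ÷ (1 − q).

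- True ratio 1.00, q = 0.05 to 0.10, intervention arm: 1.00 × 0.95 = 0.95 to 1.00 × 0.90 = 0.90.
- True ratio 0.80, intervention arm: 0.80 × 0.95 = 0.76 to 0.80 × 0.90 = 0.72.
- True ratio 0.80, control arm: 0.80 ÷ 0.95 = 0.84 to 0.80 ÷ 0.90 = 0.89.

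With the planning inputs of section 10.2, expected control events are 200 × 23.1 × 0.03 = 138.6. For no true effect and q = 0.10 in the intervention arm, expected intervention events are 138.6 × 0.90 = 124.7. The standard error of the log rate ratio is √(1/138.6 + 1/124.7) = 0.123, and |ln 0.90| ÷ 0.123 = 0.85. The two-sided 5% Wald test then rejects about 14% of the time; for q = 0.05 it rejects about 7%. This shows only that modest differential recording would matter if it occurred.

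**The case against.** The strongest reply is that nothing here is contradictory. Section 4.4.2 does not say that re-treatment staff are the only unblinded people. They are a subset of research staff, so all three statements can be true together. That stands: the conflict is one of scope, and a reader who infers a flat contradiction goes beyond the text.

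A reader might also infer that the endpoint assessors are known to be unblinded. The documents do not support this. Section 6.6 names neither the team nor the blinding of its interviewer, mothers who report symptoms are blinded, and the visit is already in the clinic registers before abstraction. Task assignment may also be set out in the Manual of Procedures or the site SOPs, which are not at hand. What remains is that 4.4.1 as written permits unblinded recording and no section of the protocol rules it out.

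On the label, participants and providers are blinded consistently and the unblinded staff are openly disclosed. Calling the double-blind description false would therefore be too strong. The label does not, however, tell the reader whether outcome recorders are blind.

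**Conclusion.** The point holds as a conflict of scope with a consequence for the primary endpoint. Section 4.4.1 unblinds research staff without limit, 4.4.2 and 5.7 name the treatment and re-treatment staff, and nobody who records temperature or symptoms, or abstracts registers, is stated to be blind. Those recorders may know the arm. This rests on reading the unspecified staff member in 6.6 as study staff, which the context favors but does not prove.

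The exposure lies mainly in temperature, symptom history and abstraction, and less in the RDT result. A reader might take the illustration to mean that the rate ratio will be shifted toward benefit by 5 to 10%. The documents give neither a size nor a direction, and the same mechanism could run the other way. The correction should be made because it is inexpensive and because analysis cannot remove differential recording later.

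**What to change.** Reword 4.4.1 to agree with 4.4.2 and 5.7, and define the staff terms once.

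- **Unblinded personnel:** the staff who perform initial treatment and re-treatment of the cloths, plus the statistician for randomization (4.4.1) and for the unblinded DSMB data (section 9). 4.4.2 should mention initial treatment as well, as 5.7 does.
- **Separation of tasks:** treatment staff do not record temperature or symptoms, perform or read RDTs, or abstract registers for the endpoint. Section 6.6 should say that the interviewer and abstractor is blinded.
- **Allocation access:** hide the REDCap allocation from all other research staff until database lock.

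The cost is less flexible rostering at the two clinics, since section 5.8 trains all staff in treating the cloths and re-treatment falls on ordinary visit days. There is also a small change at enrollment: randomization is done on a tablet, so the result must be displayed to treatment staff and not to the enrolling staff member. Sample size, endpoint and analysis model do not change.

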### Masking Procedures

Study participants and clinical providers will remain blinded to allocation of the intervention until database lock. Initial treatment and monthly re-treatment of lesus will be performed with either 0.5% permethrin or water (i.e., sham treatment) in order to maintain blinding. Study staff involved in re-treatment (permethrin or sham) of lesus will be unblinded.

## Subject Withdrawal

Participants will be followed until participant closeout, withdrawal of consent, or death. A participant may withdraw from the study at any time at his/her own request or may be withdrawn at any time at the discretion of the investigator for safety, behavioral, compliance, or administrative reasons. This is expected to be uncommon. If the participant withdraws consent for disclosure of future information, the sponsor may retain and continue to use any data collected before such a withdrawal of consent.

### Reasons for Withdrawal

Subjects are free to withdraw from participation in the study at any time upon request. An investigator may terminate a study subject’s participation in the study if:

- Any clinical AE, laboratory abnormality, or other medical condition or situation occurs such that continued participation in the study would not be in the best interest of the subject.
- The subject meets an exclusion criterion (either newly developed or not previously recognized) that precludes further study participation. This may include change of residence outside the study area.
- The subject is “lost to follow-up” defined as failure to attend three consecutive study visits and staff are unable to contact by phone or proxy.

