### Handling of Subject Withdrawals or Subject Discontinuation of Study Intervention

Given the established safety profile of the intervention there is minimal risk of continued *lesu* use outside the parameters of the study. Therefore, subjects who withdraw or otherwise discontinue participation will not be followed further.

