## Final Analysis Plan

Analyses will be conducted using an ITT approach, with woman-infant pairs analyzed according to the arm they were randomly assigned to (i.e., treated or untreated *lesu*) regardless of their subsequent use or non-use of the *lesus* and dropout. *Lesu* use will be evaluated as a secondary outcome, and if *lesu* use is lower than anticipated, exploratory analyses may use marginal structural models to estimate an “as-treated” effect of permethrin-treated *lesus* on the primary endpoint.

An α=0.05 significance level will be used throughout, with corresponding 95% confidence intervals. No adjustment for multiple testing will be made for the primary outcome. For secondary outcomes (excluding safety endpoints), we will control the false discovery rate using methods from Benjamini and Hochberg (1995).

Given the level of subject participation in the pilot study, we expect most mother-infant pairs to complete all study activities. Missing data due to dropout or missed clinic visits are anticipated to be uncommon (≤5% missing), so a complete case analysis is planned. If >10% of participants are missing data in either arm, a sensitivity analysis will be conducted using multiple imputation assuming data are missing at random (missing conditional upon measured baseline covariates and study outcomes). If data are suspected to be missing not at random, this will be described with the study results as a limitation.

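### Withdrawal for poor compliance or a later-met exclusion criterion ends outcome follow-up, which undercuts an analysis meant to hold regardless of lesu use

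*Protocol*

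**What the plan says.** **Grounds for withdrawal.** Section 4.5 says a participant "may be withdrawn at any time at the discretion of the investigator for safety, behavioral, compliance, or administrative reasons", and adds "This is expected to be uncommon". Section 4.5.1 adds, as a reason for the investigator to end participation: "The subject meets an exclusion criterion (either newly developed or not previously recognized) that precludes further study participation". Its one example is a move out of the study area.

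**The criteria that could be met later.** Section 4.2 excludes "Mother or child taking any malaria chemoprevention regimen", so the mother alone can meet this criterion. Known sickle cell disease in the child is another exclusion. The last criterion is open-ended and covers anything that would "preclude the individual’s full compliance with or completion of the study".

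**What happens next.** Section 4.5.2 says "subjects who withdraw or otherwise discontinue participation will not be followed further". Yet section 4.5 opens with: "Participants will be followed until participant closeout, withdrawal of consent, or death". That sentence does not list withdrawal by the investigator.

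**The analysis.** Section 10.3 analyses pairs in the arm assigned, "regardless of their subsequent use or non-use of the" lesus, and regardless of dropout. Section 10.2 puts everyone seen at a clinic at least once after randomisation in the primary set. Section 10.3.1 uses a Poisson model with an offset for person-time at risk.

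**The concern.** An analysis that is to hold whatever the use of the lesu needs outcomes to be observed after use stops. Sections 4.5, 4.5.1 and 4.5.2 together allow the reverse: a mother judged non-compliant can be withdrawn, and her child's later episodes are then never recorded. The same can follow when a condition on the exclusion list is recognised during follow-up. It can also follow when the mother alone meets a criterion, although the child carries the primary outcome.

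The planned analysis does not repair this:

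- The offset corrects for unequal person-time only if the end of follow-up is unrelated to risk. Withdrawal for non-use is related to it if the treated lesu works.
- Multiple imputation under section 10.3 is a sensitivity analysis, triggered only above 10% missing in an arm. It conditions on baseline covariates and outcomes, not on use.
- Replacing pairs lost before 12 weeks (section 10.2) restores numbers, not the missing outcomes.

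The exploratory work suffers too. The as-treated marginal structural models (section 10.3) and the models of incidence by frequency of use (section 10.3.1) need low users to remain under observation.

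**Working it through.** **The plan's own figures.** The protocol gives no expected number of withdrawals on these grounds and no non-user share. The nearest figures are these:

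- Mean follow-up of 23.1 of 24 weeks (section 10.2), a loss of 1 − 23.1/24 = 3.75% of person-time.
- Missing data of at most 5% (section 10.3).
- 48 of 50 pilot pairs completing (section 1.2).

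**Assumptions for the illustration.** Rate ratio 0.70 in users and 1.0 in non-users; the same underlying risk in both; share q of non-users in each arm; 23.1 weeks for everyone not withdrawn; non-users withdrawn at week w. The 28 days removed after each episode are ignored. The control rate cancels, and with equal underlying risk the control withdrawals leave the control rate unchanged.

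**Formulas.**

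- All followed: RR = (1 − q) × 0.70 + q × 1.0
- Non-users withdrawn at week w: RR = [(1 − q) × 23.1 × 0.70 + q × w] / [(1 − q) × 23.1 + q × w]

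**Example, q = 0.05 and w = 8.** All followed: 0.95 × 0.70 + 0.05 = 0.715. With withdrawal: (15.3615 + 0.40) / (21.945 + 0.40) = 15.7615 / 22.345 = 0.705. Difference: 0.010.

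| Non-users | All followed | Withdrawn week 8 | Withdrawn week 12 | RR too low by |
|---|---|---|---|---|
| 5% | 0.715 | 0.705 | 0.708 | 0.007–0.010 |
| 10% | 0.730 | 0.711 | 0.716 | 0.014–0.019 |
| 20% | 0.760 | 0.724 | 0.734 | 0.026–0.036 |

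**Against sampling error.** Planned events are 200 × 23.1 × 0.03 = 138.6 in the control arm and 138.6 × 0.70 = 97.0 in the treated arm. The standard error of the log rate ratio is √(1/138.6 + 1/97.0) = 0.132. At 5% and week 8 the shift is ln(0.715/0.7054) = 0.0136, about 0.10 standard errors. At 20% and week 8 it is ln(0.760/0.7239) = 0.0487, about 0.37.

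**A second set of assumptions.** Let non-users occur only in the treated arm, with the rate ratio fixed at 0.70 if all are followed. Withdrawing them at one quarter or one half of follow-up gives 0.688 or 0.692 at 5%, and 0.676 or 0.684 at 10%. Direction and size agree.

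**The text on duration.** Section 4.5 names three ends to follow-up: closeout, withdrawal of consent and death. Withdrawal by the investigator, in the same section and in 4.5.1, followed by no further observation under 4.5.2, is a fourth that the list leaves out.

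**The case against.** The strongest reply is that nobody leaves the analysis. A reader might infer from section 4.5.1 that randomised children are removed from the intention-to-treat set, and that the protocol so contradicts its own principle. The documents do not support that. Section 10.2 includes everyone with a clinic visit after randomisation, section 10.3 keeps pairs in their arm regardless of dropout, and section 10.3.1 uses the person-time available. Withdrawal shortens observation; it does not delete the child. The complete-case wording in section 10.3 could be read to drop partly followed children, but the explicit inclusion rule and the offset point the other way.

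The rule is also permissive, applies only where the criterion stands in the way of further participation, and is expected to be rare. Section 10.3 plans for low use and section 5.6 has antimalarial use recorded, so some such participants are evidently expected to stay under observation. No study procedure is set out for diagnosing sickle cell disease during follow-up. All this stands, and it limits the size of the problem.

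Two further inferences fail. A reader might see a conflict with section 8.4.2, under which pregnancy does not alter eligibility. The exclusion concerns a drug regimen, not pregnancy, and the protocol does not link the two. A reader might also infer that the decision to withdraw is made with knowledge of the arm. Section 4.4.1 leaves research staff unblinded, while section 4.4.2 blinds clinical providers and names re-treatment staff as unblinded. Neither says that the person deciding on withdrawal knows the allocation.

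The reply does not remove the gap in observation. Keeping a child in the set up to withdrawal does not show what happened afterwards.

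**Conclusion.** The point holds as a weakness in outcome follow-up, not as a breach of the analysis-set definition. Sections 4.5, 4.5.1 and 4.5.2 allow observation to stop on grounds that arise after randomisation and can depend on use, while section 10.3 needs those same children observed. Section 4.5 is also inconsistent with itself and with 4.5.2 on when follow-up ends.

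The expected effect on the primary estimate is small: about 0.007 to 0.010 on the rate-ratio scale at 5% non-users and 0.014 to 0.019 at 10%, in the direction of overstating benefit. This rests on assumed non-user shares, equal underlying risk in users and non-users, no protection in non-users, and withdrawal of all of them at week 8 to 12. A difference in underlying risk would change the size and could change the direction. The amendment is still worth making, because lost observation cannot be recovered at the analysis stage.

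**What to change.** Reconcile sections 4.2, 4.5, 4.5.1, 4.5.2 and 10.3:

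- **4.2:** state that exclusion criteria determine eligibility at enrolment.
- **4.5 and 4.5.1:** state that meeting a criterion later, or poor compliance with lesu use, does not by itself end scheduled visits and outcome collection to Day 168, unless consent is withdrawn or the family leaves the study area. State that a criterion met by the mother alone does not end the child's outcome follow-up. Bring the opening sentence of 4.5 on duration into line.
- **4.5.2:** separate stopping the intervention from stopping follow-up. This edit is essential, since this is the sentence that ends outcome collection.
- **10.3:** confirm that all person-time to the end of observation is analysed in the assigned arm.

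Safety and clinical-care decisions stay with the investigator; no clinical rule is proposed here.

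The cost is an amendment, which section 13.2 makes subject to ethics review, and a few more pairs kept in visits that are already scheduled. Retaining non-users dilutes the estimate slightly, which is what an intention-to-treat analysis intends.
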